### Recruitment

Patients will be selected by the outpatient department at the Clinical Unit of Physical Rehabilitation, IRCCS INRCA, in the Ancona and Fermo branches. These patients will be contacted to schedule a visit with the physician. Once the compliance with the inclusion and exclusion criteria of the study has been verified and the informed consent has been obtained in triplicate, the doctor will proceed with the baseline evaluation and with acquisition of gait assessment parameters through gait analysis at the Movement Analysis Laboratory of the Clinical Unit of Physical Rehabilitation of the Ancona branch.

A randomization technique based on a single sequence of random assignments will be used. A list of random numbers generated by the computer will be used and subjects will be assigned a number based on their order of inclusion in the study. The sequence will be saved to a password-protected spreadsheet. According to this technique, the 152 subjects will be randomly assigned to one of the 2 study groups: the control group and the technological intervention group. After the patient is assigned to one of the two groups, he will be given a code by which the physiotherapist will understand whether the patient should receive traditional or experimental treatment. The randomization was organized by using opaque envelopes: participating physicians are given randomly generated treatment allocations within sealed opaque envelopes. Once a patient has consented to enter a trial, an envelope is opened and the patient is then offered the allocated treatment group. The randomization schedule and coding of group allocations will not be accessible to the researcher conducting the assessments. According to the intention to treat (ITT) principle, subjects who were enrolled but withdrawn from the study will not be replaced. Researchers will be blinded to prevent observation bias. Statistical analyses will be conducted by a statistician, who will be blind to group allocation prior to analysis.

At the end of the treatment and after 6 months, 1 year, and 2 years, the patients will be contacted again to schedule subsequent follow-up visits and upgrades.

Recruitment will run from August 2019 to August 2021.

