### Study setting

The study will be conducted at the Clinical Unit of Physical Rehabilitation, IRCCS INRCA, in the Ancona and Fermo branches, Italy. Assessments and treatments will be conducted in the robotics laboratories.

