### Sample size

In the study of Tramontano et al. [21], the Performance-Oriented Mobility Assessment (POMA) was evaluated in two groups of stroke patients, the cases were treated through an intervention based on visual-spatial training, and the assessments were detected in 2 stages (baseline and follow-up).

POMA [22], a test widely used to assess walking ability and associated with equilibrium, was used to calculate the sample size [23]. Assuming a small effect size of 10% [24], a statistical power of 80%, a significance level of 0.05, a correlation among repeated measures of 0.5, and that sphericity is exactly met, it is estimated that the overall sample size needed to capture this effect size is of 122 subjects, two groups, and 5 repeated assessments (a baseline and 4 follow-ups) in an ANOVA model within-between interactions. Even assuming a 20% drop-out rate, the total number required would be 152 subjects (76 for each arm). The GPower (Heinrich-Heine-Universität Düsseldorf, Düsseldorf, Germany) software was used to estimate this sample size.

For the secondary outcomes, we assumed an improvement of 12% and 15% for gait speed and fear of falling, respectively. These increases have been hypothesized on the basis of articles [25, 26] that identify an improvement in these parameters using a treatment comparable to that used in this protocol.

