### Intervention

For the study, post-hospitalization subjects will be taken into consideration, after 4 weeks from the hospitalization in the Clinical Unit of Physical Rehabilitation, IRCCS INRCA, in the Ancona and Fermo branches, who have already received the standard treatment. Twenty treatment sessions will be conducted, divided into 3 training sessions per week, for 7 weeks. The control group will perform traditional therapy sessions lasting 50 min. The technological intervention group will carry out 30 min of traditional therapy and 20 min of treatment with a robotic system. Cardiac activity monitoring is planned during robotic treatments.

Individual participants must complete at least 80% of the sessions. Recovery of 3 sessions will be possible.

All patients included in the study will perform traditional rehabilitation treatments, consisted in:
Appropriate positioning in bed and chairNeuromotor treatment for the trunk control recovery and movement in bedExercises for verticalization, load balancing, and balance control from an upright positionWalking training with correct use of aidsNeuromotor treatment for the recovery of functional motility of the upper limbImproved autonomy in daily life activities with the use of aids, if necessary

The robotic treatment consists of using the G-EO system, an advanced robot-assisted, end-effector device in gait rehabilitation. The G-EO system allows to simulate both floor walking and stair climbing. The G-EO floor walking movement is generated by the motion of two footplates and allows to select different execution modality: active mode, active-assistive mode, and passive mode. The standard procedure consists of 5 sessions performed using the passive mode and 15 using the active-assistive mode. Taking into account that a personalized approach will be carried out, the therapy may be modified in based of patients’ needs. Cardiac activity monitoring is planned during robotic treatments.

Adverse events, although unlikely, could be related to the use of technology such as falls and/or pain at knees or ankles. In this case, these effects are further minimized by the presence of the lashing.

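### With one unstratified list, the stated outcome comparisons should adjust for branch and time since stroke; omitting them costs precision but causes no bias

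*Protocol article*

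**What the plan says.** In the protocol article, the Recruitment section fixes the allocation method: "A randomization technique based on a single sequence of random assignments will be used", and "subjects will be assigned a number based on their order of inclusion in the study". It names no block, stratum or minimisation factor. Allocations are handed to physicians in sealed opaque envelopes.

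The Study setting section places the trial "in the Ancona and Fermo branches, Italy". Under Participants, the stroke must have occurred no more than 3 months before recruitment. Under Intervention, patients are taken "after 4 weeks from the hospitalization in the Clinical Unit of Physical Rehabilitation". That lower limit counts from admission to the rehabilitation unit, not from the stroke.

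The Sample size section states that "the total number required would be 152 subjects (76 for each arm").

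The Data analysis section compares outcomes between groups by independent-samples t-tests and chi-squared tests, repeated at each time point. Repeated-measures mixed models with interactions follow. It does not say which of these carries the inference, and it names no covariate. Table 2 has no row for time since stroke.

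**The concern.** Patients can enter at quite different points of early recovery. Two patients with the same POMA score at 5 and at 12 weeks may have different expected recovery, so baseline POMA does not fully stand in for time since stroke. A single list balances neither time since stroke nor branch except on average, and an unadjusted t-test leaves the variation due to both in the error term.

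Two things are at stake. The first is precision, in a design planned at 80% power with little to spare. The second is interpretation: if the arms happen to differ in time since stroke, an unadjusted result is hard to read, and an adjustment chosen after the imbalance is seen carries less weight than one fixed beforehand.

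**Working it through.** **The plan's own figure.** Inputs (Sample size section): "Assuming a small effect size of 10% [24], a statistical power of 80%, a significance level of 0.05", correlation 0.5, sphericity, two groups, five assessments. Reading the 10% as f = 0.10, the within-between interaction has noncentrality f²·N·m/(1 − ρ) = 0.01 × 122 × 5 / 0.5 = 12.2, with 4 and (122 − 2) × 4 = 480 degrees of freedom. Power is 0.805 at N = 122, so the figure reproduces. Drop-out: 122 / 0.8 = 152.5, stated as 152. Stratification does not enter this calculation.

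**Chance imbalance in time since stroke.** Assumption: entry uniform over 4 to 13 weeks.
- SD = 9/√12 = 2.60 weeks.
- SE of the difference in means, 76 per arm = 2.60 × √(2/76) = 0.42 weeks. The 95% limit is 1.96 × 0.42 = 0.83 weeks, or 0.32 SD.
- With 61 per arm after drop-out the limit is 0.92 weeks, or 0.35 SD.
- If delay before admission to the unit narrows the window to, say, 6 to 13 weeks: SD = 7/√12 = 2.02, and the limit with 76 per arm is 1.96 × 2.02 × √(2/76) = 0.64 weeks.

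**Chance imbalance in branch.** The 95% limit is 1.96 × √(p(1 − p) × 2/76), which is 13 to 16 percentage points for an assumed larger-branch share p of 80% to 50%.

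**Shift in the outcome at the 95% limit, 61 per arm.** Shift = r × 0.355 SD, where r is the assumed correlation of time since stroke with outcome.

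| r | Shift (SD) | Share of d = 0.5 | Share of d = 0.2 |
|---|---|---|---|
| 0.2 | 0.07 | 14% | 35% |
| 0.3 | 0.11 | 21% | 53% |
| 0.5 | 0.18 | 35% | 89% |

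Here d = 0.5 is roughly what 61 per arm can detect with 80% power in a t-test, and d = 0.2 is f = 0.10 read as a two-group difference. If the 10% means 2.8 of the 28 POMA points, with an assumed SD of 4 to 7, the shift is 0.3 to 1.2 points for r = 0.2 to 0.5, or 10% to 44% of the effect.

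**Type I error and power.** Simulation with N = 122, 6000 runs, d = 0.5, an assumed 70% share for one branch, and no baseline POMA in the model. Stratified lists used blocks of 4 by branch and by time since stroke.

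| Design and analysis | Type I error, r = 0.3 | Power, r = 0.3 (branch 0.15) | Power, r = 0.5 (branch 0.20) |
|---|---|---|---|
| Single list, unadjusted | 0.047 | 0.775 | 0.788 |
| Single list, adjusted | 0.049 | 0.822 | 0.896 |
| Stratified, unadjusted | 0.036 | 0.788 | 0.811 |
| Stratified, adjusted | 0.043 | 0.823 | 0.905 |

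Monte Carlo error of a power near 0.8 is √(0.8 × 0.2/6000) = 0.005.

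A normal approximation agrees. The unadjusted SE is √(2/61) = 0.181, giving power Φ(0.5/0.181 − 1.96) = Φ(0.80) = 0.79. At r = 0.3 the adjusted SE is 0.181 × √(1 − 0.09 − 0.0225) = 0.171, giving Φ(0.97) = 0.83. At r = 0.5 it is 0.181 × √(1 − 0.25 − 0.04) = 0.153, giving Φ(1.32) = 0.91.

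**Arm sizes.** If the list is unrestricted, one arm has a 95% range of 64 to 88, exactly 76/76 has probability 6.5%, and 68/84 or worse has probability 22%. The relative efficiency of 68/84 is 4 × 68 × 84 / 152² = 0.989, a loss of about 1%.

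**The case against.** Simple randomisation of 152 patients is an accepted design. It is unbiased, and chance imbalance is already counted in the standard error. That stands: the single list analysed without adjustment keeps its type I error at 0.047 (r = 0.3).

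A covariate list is commonly left to the statistical analysis plan, which is not shown and may already name these terms. That also stands, so silence about covariates is not the point. What the article does state is a single list and t-tests on the outcomes, and these are what the point addresses.

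A reader might infer more than the documents support, in three ways.
- **That imbalance could mimic or mask the whole effect.** With 61 per arm, the chance of a shift as large as 0.2 SD, the smallest reading of the effect, is below 0.001 for r up to 0.3 and 2.7% at r = 0.5. Nor can the imbalance in weeks simply be multiplied by a weekly recovery rate. With an assumed 0.3 to 1.0 POMA points per week that gives 0.83 × 0.3 = 0.25 to 0.83 × 1.0 = 0.83 points. Over a course of fixed length, however, later entry alters change from baseline only by the difference between the recovery rates at its start and end. With a constant rate the shift is zero, so those products are an upper bound.
- **That each branch has its own therapists, and so a therapist effect.** The article does not describe staffing by branch.
- **That the trial must be re-stratified.** Once the analysis adjusts, stratifying moves power from 0.822 to 0.823, or from 0.896 to 0.905. Changing envelopes in mid-trial needs an amendment and, with small blocks, adds some predictability.

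**Conclusion.** The point holds as one of efficiency and robustness, not validity. An unstratified list combined with unadjusted comparisons gives up precision that could be had almost free. Adjustment is worth roughly 5 points of power at r = 0.3 and 11 at r = 0.5, with branch correlations of 0.15 and 0.20 included. For time since stroke alone, the gain is equivalent to 1/(1 − r²) times the patients: 1.04 at r = 0.2, 1.10 at r = 0.3 and 1.33 at r = 0.5.

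The correlations, d = 0.5, the branch share, the POMA SD and the uniform entry window are all assumptions; the article gives none of them. The correlation that matters is the one remaining after baseline POMA is in the model. If that is weak, the gain is small: at r = 0.1 the factor is 1.01.

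The figure of 76 per arm is best read as a planned split. It is not guaranteed unless the list is blocked or has a fixed total, and the cost of missing it is slight.

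**What to change.** - **Analysis, for all patients.** Make the repeated-measures model the basis for inference on POMA between groups, with baseline POMA, branch, and weeks since stroke at entry as prespecified fixed terms. If baseline POMA is a covariate, only the four post-baseline visits enter as outcomes. The t-tests can stay as description. Fix this before allocation is revealed to the statistician; if the analysis plan already says so, bring the Data analysis section into line.
- **Data.** Carry the stroke date into the trial database. It is already needed to check the 3-month criterion.
- **Wording.** Describe 76 per arm as planned, or state that the list is blocked or has a fixed total.
- **Optional.** For the remaining patients, use permuted blocks of varying size stratified by branch. This would also settle how one sequence in order of inclusion works with envelopes held at two branches. Recruitment had begun, so it needs a documented amendment, for about 0 to 1 point of power.

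The main cost is two model terms beyond baseline POMA. The downside is a smaller gain if time since stroke adds little once baseline POMA is known.

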### Intervention

For the study, post-hospitalization subjects will be taken into consideration, after 4 weeks from the hospitalization in the Clinical Unit of Physical Rehabilitation, IRCCS INRCA, in the Ancona and Fermo branches, who have already received the standard treatment. Twenty treatment sessions will be conducted, divided into 3 training sessions per week, for 7 weeks. The control group will perform traditional therapy sessions lasting 50 min. The technological intervention group will carry out 30 min of traditional therapy and 20 min of treatment with a robotic system. Cardiac activity monitoring is planned during robotic treatments.

Individual participants must complete at least 80% of the sessions. Recovery of 3 sessions will be possible.

All patients included in the study will perform traditional rehabilitation treatments, consisted in:
Appropriate positioning in bed and chairNeuromotor treatment for the trunk control recovery and movement in bedExercises for verticalization, load balancing, and balance control from an upright positionWalking training with correct use of aidsNeuromotor treatment for the recovery of functional motility of the upper limbImproved autonomy in daily life activities with the use of aids, if necessary

The robotic treatment consists of using the G-EO system, an advanced robot-assisted, end-effector device in gait rehabilitation. The G-EO system allows to simulate both floor walking and stair climbing. The G-EO floor walking movement is generated by the motion of two footplates and allows to select different execution modality: active mode, active-assistive mode, and passive mode. The standard procedure consists of 5 sessions performed using the passive mode and 15 using the active-assistive mode. Taking into account that a personalized approach will be carried out, the therapy may be modified in based of patients’ needs. Cardiac activity monitoring is planned during robotic treatments.

Adverse events, although unlikely, could be related to the use of technology such as falls and/or pain at knees or ankles. In this case, these effects are further minimized by the presence of the lashing.

### Outcomes

All outcome measures follow a standardized operating procedure. Table 1 shows the primary outcome and the secondary outcomes with the expected result at the end of the treatment. The expected improvement was derived from the analysis of similar studies [24], collected for the evaluation of the sample size for each outcome.

**Table 1 Tab1:** Outcomes and clinical assessments

Outcome(s)	Clinical assessment	Expected improvement at the end of treatment (%)
Primary: Decrease of falling risk	POMA	10
Secondary: Gait improvement (increase in walking speed)	Gait speed (gait analysis)	12
Secondary: Decrease of fear of falling	FES-I Short form	15

*POMA* Tinetti’s Scale or Performance-Oriented Mobility Assessment, *FES-I* Short Falls Efficacy Scale—International

Further evaluations will be carried out as follows:
Length and asymmetry of the semi-step, through instrumental gait analysisWalking and functional status through the Functional Ambulation Category and Barthel Index scaleAcceptance of the technology, through a UTAUT questionnaire

A summary of all data collected and when these are collected is provided in Table 2.

**Table 2 Tab2:** Schedule of assessment and outcome measures

Outcome	Clinical assessment	R	T1	FW1	FW2	FW3
Cognitive state	Mini-Mental State Examination	✓				
Gait parameters	Functional Ambulation Category	✓	✓	✓	✓	✓
Disability state	Rankin Scale	✓				
Cognitive state	CDR	✓				
Functional state	Barthel Index	✓	✓	✓	✓	✓
Spasticity state	Modified Ashworth scale	✓				
Quality of life	SF-12 Health Survey	✓	✓	✓	✓	✓
Sociodemographic characteristics	Check-list	✓				
Motor ability	Motricity index	✓	✓	✓	✓	✓
Attitude to technology	Assistive Device Predisposition Assessment – Scala E	✓				
Fall risk	Scala di Tinetti	✓	✓	✓	✓	✓
Gait parameters	Gait analysis + instrumental postural analysis	✓	✓	✓	✓	✓
Fear of falling	Short Falls Efficacy Scale—International	✓	✓	✓	✓	✓
Acceptance of technology	Psychosocial Impact of Assisted Device Scale (PIADS)		✓			

*R* recruitment, *T1* end of treatment, *FW1* first follow-up at 6 months since the end of treatment, *FW2* second follow-up at 1 year since the end of treatment, *FW3* third follow-up at 2 years since the end of treatment

#### Mini-Mental State Examination (MMSE)

The MMSE was designed as a clinical method for grading cognitive impairment. The score ranges from 0 to 30: scores ≥24 indicate normality, between 18 and 23 indicate mild cognitive impairment, between 11 and 17 average cognitive deficits, and scores ≤10 severe cognitive impairments. The reported score is corrected for age and education [27].

#### Rankin Scale (RA)

It is a simple scale for the evaluation of the outcomes following the stroke. Reliability is well defined. The individual categories are essentially based on patient mobility. There are 6 grades of classification from 0 to 5, where 0 means independence [28].

#### Barthel Index (BI)

BI is an ordinal scale used to measure a subject’s performance in everyday life activities. The index analyzes ten variables that describe the activities of daily life and mobility. Each item is assigned a score between 0 and 10 depending on the degree of patient’s functionality: full, reduced, or no functionality. A high overall score is associated with a greater probability of being able to live at home independently after discharge from the hospital [29].

#### Functional Ambulation Categories (FAC)

The scale is used to classify the severity level of gait disturbances in neurological disorders. It provides a hierarchical classification from level 0 (impossible walking) to level 5 (no limitation) [30].

#### Modified Ashworth scale (SA)

The scale carries out the assessment of spasticity/hypertonus. The scores range from 0 to 4, 0 no spasticity and 4 rigid limbs in flexion or extension [31].

#### SF-12 Health Survey (SF-12)

The SF-12 questionnaire was originally developed in the USA to provide a short alternative form to the SF-36 questionnaire. The SF-12 is composed of 12 items that produce two measurements related to two different aspects of health: physical health and mental health. The subject is asked to answer on how he feels and how he is able to carry out the usual activities, evaluating the current day and the 4 previous weeks [32].

#### Tinetti’s Scale or Performance-Oriented Mobility Assessment (POMA)

Tinetti scale is a tool used to evaluate balance and gait performance. The test is used clinically to determine the mobility status of a subject or to assess changes in balance and gait time. The total POMA (POMA-T) consists of two sub-scales: the balance evaluation scale (“balance scale” or POMA-B) and the gait evaluation scale (“gait scale” or POMA-G). The maximum score is 28 points: in detail, the maximum score of the POMA-B is 16, while for the POMA-G the maximum score is 12 [22].

#### Motricity index (MI)

The scale shows a significant correlation between lower limb scores and dynamometric measurements. The total score ranges from 0 to 100. It provides 3 items with a score between 0 and 33: 0 no movement, 33 movement performed with normal force [33].

#### Short Falls Efficacy Scale—International (FES-I-Short)

The scale measures the “fear of falling.” The scale can be self-administered or administered during the interview. The cutoffs for the fear of falling are divided as follows: a score between 7 and 8 indicates a low concern, between 9 and 12 a moderate concern, and between 14 and 28 a high concern [34].

#### Psychosocial Impact of Assistive Devices Scale (PIADS)

It is a self-completed questionnaire by the user and it assesses the impact that the device has on the person. Through 26 questions, it tries to detect how the device has brought about a perception of change with respect to one’s availability for new experiences (6 questions), skills (ability to cope with daily activities and challenges—12 questions), and self-esteem (security and self-confidence—8 questions). Every question is answered on a visual scale marked by −3 (the device has strongly limited my independence) to + 3 (the device has greatly improved my independence) [35].

#### Assistive Device Predisposition Assessment (ATDPA)

The purpose of the tool is to assess user expectations about technological devices [36].

#### Clinical Dementia Rating Scale (CDR)

This questionnaire assesses the patient’s dementia status. The CDR is a 5-point scale used to characterize six domains: memory, orientation, judgment and problem solving, business, home and hobby, and personal care [37].

#### Gait analysis and instrumental postural analysis

Gait analysis is the systematic study of human locomotion, augmented by instrumentation for measuring body movements, body mechanics, and the activity of the muscles [38]. Gait analysis is performed on the selected patients at the Gait Analysis Laboratory in the Department of Physical Rehabilitation at branch of IRCCS INRCA Ancona. Instrumented gait analysis is performed using BTS GAITLAB (BTS Bioengineering, Italy) system with six infrared cameras (100 Hz) and 2 force plates (50 Hz). The system is used to acquire both kinematic and kinetic data. Three-dimensional kinematic data are recorded with the help of 22 reflective infrared markers using Helen Hayes protocol [39]. The floor-mounted force plates are used to acquire the kinetic data. The subjects walked at a self-selected speed. The instrumental postural analysis studies the complex control system that must keep the center of gravity constantly in a balanced position. This analysis is carried out through an advanced system composed of a camera for video recording and a platform with 2 triaxial sensory plates (Podium, BTS Bioengineering, Italy). With this system, it is possible to simultaneously visualize the three components of force: vertical, antero-posterior, and lateral. It allows to evaluate, in augmented reality, the symmetry of the load and the trend of the pressure center.

